**Figure 2 F2:**
[figure not shown]
**Screen shots of ColoDATES Web (Figures **2**A-****2E).**

**Figure 3 F3:**
[figure not shown]
Structural equation model.

### CW and SW data retrieval protocol

For both CW and SW, the following data will be retrieved: time from login to logoff; frequency/duration each screen page was accessed; CRCS test option selected.

### Patient post-web survey

The survey (see Additional file 3 for the actual survey; completion time: ten minutes) will be administered online immediately after the DA intervention (CW or SW). The survey will assess patient’s knowledge, attitude, subjective norm, and perceived self efficacy about CRC screening; preferred CRC screening test option; and intent to get screened for CRC. It will also include manipulation-check questions to assess what components of CW were most helpful for the patients in selecting a CRCS test option.

### Linking the summary page to the patient’s clinic visit

The research assistant will have a portable printer to ensure that the Summary Page is provided to the patient and clinician prior to the appointment. Clinicians will not be aware of which arm (intervention arm or control arm) the patient will be in since patients from both arms will have a printed Summary Page, formatted in such a way that it is not clear which Summary Page constitutes the intervention arm and the control arm.

It should be noted that the clinicians are free to make their own recommendation, and should they disagree with the patient’s choice of CRCS test option, may recommend another option. This may occur when a patient prefers a CRCS test other than colonoscopy, since clinicians increasingly prefer colonoscopy for CRCS, as shown in previous studies [35,36], our preliminary survey to the primary care practices, and a recent state-wide survey of Michigan physicians [67]. However, current guidelines do not recommend colonoscopy over other CRCS options [1,3], and ultimately, due to lack of colonoscopy access, insurance, and other reasons including patient preference, a CRCS test other than colonoscopy may be selected.

### Digital audio recording of patient-clinician encounter/OPTION scale

Both intervention and control arms will undergo audio recording. The research assistant will place a small digital audio recorder in the examination room just before the patient/clinician encounter, turn it on, and leave the room. During the encounter, the patient or clinician can turn off the digital audio recorder at any time to block recording of sensitive discussions. It may be turned back on once the sensitive discussion is completed. At the end of the encounter, the research assistant will retrieve the recorder, turn it off, remove the media, record on the data sheet, and upload the data to a secure server with the corresponding code. The investigators (PI, project manager, and three co-investigators) will read all transcripts to assign an Observing Patient Involvement (OPTION) score. The OPTION scale (see Additional file 4 for the actual form) is a validated 12-item instrument considered to be the most efficient and sensitive SDM coding system for research purposes [68-71]. Because the OPTION scale focuses on a single agenda during a patient-clinician encounter, and assesses to what degree clinicians involve patients in SDM, it is well suited to assess how the patient activated by CW affects the clinician’s SDM performance. The trained observers will listen to the audio recorded portion of the visit pertaining to CRCS and assign raw scores for each of 12 constructs in SDM, which will be converted to a scale of 0 to 100, with 0 indicating minimum and 100 indicating maximum degree of SDM. The observers will be blinded to the study arm (intervention arm or control arm) assignment, patient name, clinician name, and clinical site. The audio recording occurs in both study arms; therefore, no observational bias would be introduced into the comparison of the study arm interventions.

### Patient post-encounter survey

The research assistant will administer this survey (see Additional file 5 for the actual survey; completion time: five minutes) by paper to the patient after the patient-clinician encounter. The survey will assess patient’s preferred CRCS test; whether concordance was achieved with the clinician (that is, whether the clinician's final CRCS test recommendation matched the patient’s preferred CRCS test option); whether the patient felt his/her role in deciding to get checked for CRC was just right, tilted too much towards the clinician or too much toward the patient; and intent to undergo screening for CRC.

### Administering the endpoint chart audit and survey

Six months from the patient visit, the chart will be audited by the research assistant (see Additional file 6 for the actual audit form). Information on CRCS available in the medical chart will include stool blood test, flexible sigmoidoscopy, double contrast barium enema, computerized tomography colonography, and colonoscopy. Further, we will ascertain follow-up procedures used with patients who have an abnormal CRCS test result. Patients without medical record documentation will be called to check whether or not CRCS had been done and, if so, type of test and by which clinician/practice. If the clinician/practice identified is outside of the participating clinician/practice of the study, we will obtain a release of information for medical records from these outside sites to confirm the self-report. If a release is not provided or medical records cannot confirm the self-report, the patient will be coded as not having completed CRCS. The only acceptable outcome endpoint will be a medically documented CRCS procedure. Self-report of completing CRCS with no documentation, and self-report of not completing CRCS, will be coded as no CRCS done [72-79]. Documented incomplete CRCS test (for example, unsuccessful colonoscopy, incomplete number of stool blood cards submitted) will be coded as incomplete CRCS. Thus, there will be no missing data for this outcome endpoint. In addition to ‘CRCS done’, ‘CRCS incomplete’, and ‘CRCS not done’, information on the type of CRCS test done will be collected.

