### Patient population and eligibility criteria

The number of participants recruited per practice will be proportional to the practice size. African Americans will be overrepresented to comprise 25% of the total patient number (75 patients per arm). Patients are eligible for the study if aged between 50 and 75 years; complete their address and telephone number; are scheduled for a health maintenance examination or a chronic care visit; have not undergone a current CRCS procedure (stool blood test within the past year, flexible sigmoidoscopy within the past five years, double contrast barium enema within the past five years, computerized tomography colonography within the past five years, colonoscopy within the past ten years); have no dementia or psychosis; have no history of CRC; have no medical contraindication to CRCS; are able to read and write English; are able to give informed consent. The research assistant designated to each practice will review medical records and prepare a list of eligible patients. The practice clinicians will review the list and exclude those that should not be contacted and why. Each patient will receive an honorarium of US$25 at the completion of the study intervention.

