### Randomization of the patients to the intervention arm and the control arm

After completing the patient baseline survey, the computer program will randomize the patients into the intervention arm and the control arm. The randomization will be stratified by practice, gender, and race to ensure there are equal proportions of patients by these factors in both arms.

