### Delivery of the DA intervention (CW/SW)

After randomization, the participating patients will enter the introductory page for CW for those randomized to the intervention arm and SW for those randomized into the Control Arm. In the intervention arm, the patients will access and work through CW. On entering CW, the patient will be guided to Overview, then Personal Risk Assessment, where they will interactively answer questions about their personal and family health history. There will be immediate feedback on whether they are ‘Average Risk’, ‘Increased Risk’, or ‘Unknown Risk’ (this occurs if the patient, who is otherwise average risk, answers ‘I don’t know’ to any of the questions in the Personal Risk Assessment). Next, the patients will be guided to access the Comparison Table providing information on CRCS tests (see Figure 2) and a Preference Clarification Tool from which they may select the three most important issues of a CRCS test (see Figure 3). The test most closely matching the three selected issues will be provided. The patients may work on the tool for as long as they wish. Once they select the matched test, a Feedback Page reviewing their test of choice in the context of their risk will be provided: ‘Average Risk’, ‘Increased Risk’, or ‘Unknown Risk’. The combination of patient risk profile and preference will help the patients to understand the details of CRCS, how each test correlates with their preference, their risk for CRC, and how their preference may or may not match the recommended test based on their risk. They will be given a final opportunity to select a CRCS test based on their risk and preferences. Once they submit their choice, a Summary Page will appear that shows them: their risk, their three most important issues, CRCS test based on the three issues, and the test they ultimately selected. Participating patients in both intervention and control arms will undergo the intervention in a private room. For patients needing help using the computer, the research assistant will provide this support but will not counsel them on CRCS. These provisions will ensure privacy, standardization, and inclusion of patients without Internet access and low computer literacy and skills.

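### The six-month screening outcome is audited by a role that can learn the arm, with no blinding stated for it, and every failed confirmation counts as not screened

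*Protocol article*

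**What the plan says.** All references are to the Protocol article.

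- **Who audits.** *Administering the endpoint chart audit and survey*: "Six months from the patient visit, the chart will be audited by the research assistant".
- **What else that role does.** *Patient population and eligibility criteria*: "The research assistant designated to each practice will review medical records and prepare a list of eligible patients". *Patient recruitment and consent* has the assistant telephone patients and obtain consent. *Delivery of the DA intervention (CW/SW)*: "For patients needing help using the computer, the research assistant will provide this support but will not counsel them on CRCS". In *Linking the summary page to the patient's clinic visit* the assistant handles the printout: "The research assistant will have a portable printer to ensure that the Summary Page is provided to the patient and clinician prior to the appointment". The assistant also gives the post-encounter survey.
- **Allocation.** *Randomization of the patients to the intervention arm and the control arm*: "the computer program will randomize the patients into the intervention arm and the control arm". The websites deliver the two interventions.
- **Who is blinded.** The Abstract names clinicians and analysts. The section on audio recording adds the OPTION observers, who are masked to arm, patient, clinician and site. No such sentence covers the chart audit.
- **How the outcome is coded.** Patients with nothing in the chart are telephoned. If they report a test elsewhere, a release and the outside record are sought. Only a documented procedure counts. Self-report without documentation is coded as no screening, and a documented incomplete test has its own code. The section concludes: "Thus, there will be no missing data for this outcome endpoint".

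**The concern.** The article masks the rating of shared decision making in detail, yet states no masking for the assessor of screening uptake, the outcome that drives the sample size.

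Reading a chart for a documented procedure leaves little room for judgement. The steps after it leave more: whether the patient is reached, whether a release is obtained, whether the outside practice replies, and whether a test is called complete or incomplete. Failure at any of the first three lands in the same category as a patient who was truly not screened. Patients who are never reached are not mentioned by name, but a rule that accepts only documentation and leaves nothing missing puts them there too.

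The absence of missing data is therefore produced by the coding rule and does not show that ascertainment was complete. If calls and releases were pursued harder in one arm, that arm's screening rate would rise. The yes/no outcome in the Aim 1 analysis would carry no trace of it, and the section on missing data deals with covariates only.

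**Working it through.** **1. The plan's own figure.** Inputs from *Sample size and power*: 24% in control, an increase of 15 points (to 39%), two-sided 5%, 90% power, continuity-corrected chi-square. This gives 213 per arm, exactly as stated (200 without the correction). At 150 per arm the corrected power is 76.5%, against 76% stated. The design arithmetic is sound, and the point below changes neither the 213 needed nor the 300 planned.

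**2. Model for ascertainment.** Let p be the true completion rate in an arm, f the share of completions that are not in the practice chart and so need the call and release, and c the share of those that are confirmed. Then

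observed rate = p × (1 − f + f × c).

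The article gives neither f nor c. Every value of them below is an assumption.

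**3. No true effect, unequal confirmation.** Spurious difference = p × f × (c in intervention − c in control). Rejection rates are for the uncorrected two-sided z test at 300 per arm.

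| p | f | c, intervention vs control | Spurious difference | Rejection rate |
|---|---|---|---|---|
| 24% | 10% | 90% vs 70% | 0.24 × 0.10 × 0.20 = 0.48 points | 5.2% |
| 24% | 20% | 90% vs 70% | 0.24 × 0.20 × 0.20 = 0.96 points | 5.9% |
| 39% | 20% | 90% vs 70% | 0.39 × 0.20 × 0.20 = 1.56 points | 6.8% |
| 39% | 40% | 90% vs 70% | 0.39 × 0.40 × 0.20 = 3.12 points | 12.5% |
| 39% | 40% | 90% vs 50% | 0.39 × 0.40 × 0.40 = 6.24 points | 36.3% |

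The second row is taken as the typical case. The last row is an extreme: it needs both a high dependence on the call and a 40-point gap.

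A simpler form works with all patients: shift = (share with outside-only tests) × (confirmation gap). With 5% to 15% and 10 to 20 points, this is 0.05 × 0.10 = 0.5 points to 0.15 × 0.20 = 3 points.

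**4. True effect as designed (24% vs 39%).** Power is continuity-corrected at 300 per arm.

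| c, intervention vs control | Observed difference, f = 10% to 40% | Power |
|---|---|---|
| 70% vs 70% | 14.6 to 13.2 points | 97% to 94% |
| 50% vs 50% | 14.3 to 12.0 points | 96% to 91% |
| 90% vs 70% | 15.3 to 16.3 points | 98% to 99% |
| 90% vs 50% | 15.8 to 18.2 points | 99% or more |
| 70% vs 90% | 14.1 to 11.3 points | 96% to 84% |

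Equal under-ascertainment costs a little of the effect and leaves power at 91% or more. Only a gap between arms inflates or creates a difference, and the gap can run in either direction.

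**The case against.** A reader might infer that an unblinded assistant delivers the intervention and then audits the same patients with more zeal in one arm. The article does not support that.

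- A program allocates and a website delivers. The assistant gives computer help only where needed and does not counsel.
- Both arms get a Summary Page formatted so that the arm is not clear. That sentence concerns clinicians, but printing the page does not by itself reveal the arm. Arm knowledge is a fair inference for patients who were helped, since the control website lacks the interactive tools. For the others it is only possible.
- The article names a role for the audit and does not say that the same individual does it. It does not say who makes the calls or requests the releases. Attachment to a practice makes the same person likely, no more.
- The endpoint needs medical documentation, an audit form exists, and the call is triggered by an empty chart whatever the arm. Nothing suggests that effort differs.
- Caller identity and call logs may well sit in fuller procedures that are not shown. The Aim 1 analysis does compare arms on data completion, though it does not say whether this includes the follow-up call.
- The upper assumption is strained: 15% of all patients with outside-only tests would be 0.15 / 0.24 = 62.5% of completions at the control rate, in patients who all have a primary care clinician.

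These objections remove any claim of demonstrated bias. They do not remove the gap, because the article itself says who audits, who is blinded, how failed confirmation is coded and that nothing is missing.

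**Conclusion.** The point holds as a weakness of method that is cheap to repair. The primary outcome is collected by a role with access to arm information and with no stated masking, through steps that depend on effort, under a coding rule that merges failed follow-up with no screening.

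The documents do not show that the auditor knows every patient's arm, that follow-up will differ, or in which direction. Nor do all patients without a confirmed completed test become *not done*, since documented incomplete tests are coded separately.

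The size rests wholly on assumed values of f and c. A plausible range is roughly 0.5 to 3 points, with about 1 point and a 5.9% rejection rate in the typical case. This is modest beside the 15-point target and matters most if the true effect is small. If ascertainment is equal, the rule is conservative.

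**What to change.** 1. State that the audit, telephone calls, release requests and complete/incomplete coding are done from a list that does not show the arm. Where feasible, use an existing team member who did not run that patient's visit, for example by exchanging practices between assistants.
2. Fix the same steps for both arms: the trigger for a call, the number of attempts, and the handling of releases and outside records.
3. Replace the statement that no data are missing with counts per arm of patients documented in the chart, called, reached, self-reporting a test, giving a release, confirmed, unconfirmed and not reached.
4. Keep documented screening as the primary endpoint. Counting unconfirmed self-reports as done may be added as a supplementary analysis, but it leaves patients never reached as not screened and so cannot detect unequal pursuit of them. The counts in item 3 are what make that visible.

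The cost is some re-assignment of staff between practices, subject to the data sharing agreements (terms not shown), time to learn another practice's records, and one extra table. The sample size does not change. *Trial status* gives 339 of 600 recruited on 28 October 2013, so at that date at least 600 − 339 = 261 planned patients still had their audit ahead of them. If audits already done were not masked, that should be reported.

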### Data collection instruments

Table 2 summarizes the data collection instruments with respect to source and time point of collection. Post-web survey will include manipulation-check questions. Also, data regarding patient’s CW/SW usage will be retrieved. They will allow us to check whether the patients in the intervention arm actually used the interactive tools in CW and found them to be useful. A more detailed table that correlates each question of the surveys with the domains of the conceptual model is included in Additional file 7.

**Table 2 T2:** Mediators and outcomes and data collection points

	**Patient survey**			**Clinician survey**	**Digital audio recording of patient visit**	**Endpoint chart audit**
	**Baseline**	**Post**-**web**	**Post**-**encounter**			
Demographic data (BRFSS)	×			×		
Past experience	×					
Knowledge	×	×				
Attitude	×	×				
Subjective norm	×	×	×			
Perceived self efficacy	×	×				
Patient preference	×	×	×			
Manipulation-check questions		×				
Clinician decision making Style				×		
Shared decision making			×		×	
Concordance			×		×	
Patient intention	×	×	×			
Action (CRCS)						×
Method of collection	web	web	paper	paper	recording	medical chart

x: Signifies that the mediators and outcomes in question were addressed in the survey, recording or audit.

### Analysis

In the year following the end of six-month chart audit (April 2015 to March 2016), we will complete data analyses to test study hypotheses.

### Aim 1: to measure the impact of CW on patient uptake of CRCS

H-1: patients in the intervention arm will have higher rates of CRCS adherence at the six month follow-up than those in the control arm.

The study arms will be compared to assure that randomization achieved similar study population with respect to age, gender, race, previous CRCS, practice site, and data completion. Medically documented completion of CRCS will be compared between the intervention arm and the control arm by means of a chi-square test (unadjusted analysis) and a logistic regression adjusting for potential predictors at baseline. The regression analysis will be performed with data at the patient level with completing CRCS (yes/no) as the outcome measure and the arm assignment (intervention arm versus control arm) as the main covariate of interest. The practice indicator will further be included as a covariate in order to account for the variation between practices. The clustering effect due to clinician will be accounted for by using a generalized estimating equations approach. Personal patient-level background information (for example, age, race, education, marital status, smoking, health status, health insurance) from the patient baseline survey will be considered for inclusion in the regression model. The model will further be adjusted for information about the patient’s past experience with the CRCS procedures and the baseline level of patient determinants (for example, knowledge, attitude, subjective norm, self-efficacy) and intent. We will also adjust for OPTION score and pertinent clinician-level covariates such as the clinician’s communication style from the clinician survey. In order to understand whether there is any difference in the completion of CRCS rates between groups of patients who (a) complete the risk assessment tool only, (b) complete the preference clarification tool only, (c) complete both, and (d) complete neither, we will use a four level factor indicating this group membership as an independent variable in the regression model.

The contribution of a specific group of covariates will be measured by means of increase in generalized R-square defined as:$$R^{2}\left(\mathrm{increase}\right)=\exp\left(-L_{1}^{2}/n\right)-\exp\left(-L_{2}^{2}/n\right)$$where $L_{1}^{2},L_{2}^{2}$ are the likelihood ratio statistics of the smaller and larger models, respectively.

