Our proposed project, Decision Aid to Technologically Enhance Shared decision making (DATES), will test CW’s effectiveness for increasing CRCS and its facilitation of SDM in primary care practices through rigorous analysis of a conceptual model adapted from the Theory of Planned Behavior [49-53] (See Figure 1). It provides a framework that clarifies the relationship between DAs and SDM [54,55]. The theory incorporates three patient determinants (attitude, subjective norm and perceived self-efficacy) that influence patient intention, which in turn influences patient behavior. In our conceptual model, we have added knowledge to patient determinants, since DAs increase knowledge [56,57]. Additionally, based on our pilot randomized controlled trial, we believe that the patient’s preference toward a specific CRCS test option is a key mediator between CW and patient intention to undergo screening for CRC. Thus, interaction with CW positively affects patient determinants, leading to the patient establishing a preference for a particular CRCS test option. This leads to greater patient intention to undergo screening and ultimately, higher CRCS rate. This process is also mediated by what occurs between the patient and the clinician during the clinic visit to discuss CRCS: the degree of SDM reached and whether the patient and the clinician agree on which CRCS test option to choose. The latter will be termed concordance.

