### Variable selection

In view of a potentially large number of candidates for inclusion as covariates, we will use a simple screening method as follows. Each potential covariate will be investigated for *confounding* effect by running a preliminary screening analysis with and without the covariate in the model along with the study arm and retaining the ones for the final logistic regression model, which either: (a) have a significant effect on the outcome; or (b) change the co-efficient of the study arm variable by more than 5%. *Moderating* effect of a potential covariate × will be investigated by including a study arm × interaction term in the model.

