### Aim 3: to evaluate the impact of CW on SDM, concordance, and patient intention during and after the patient-clinician encounter

H3-1: patients in the intervention arm will experience a higher level of SDM than those in the control arm.

H3-2: higher rates of concordance will be reached between the patient’s preferred CRCS test and the clinician’s recommended CRCS test in the intervention arm than those in the control arm.

H3-3: patient’s intention to undergo CRCS after the patient-clinician encounter will be predicted by the study arm, degree of SDM, concordance, and interaction between SDM and concordance.

We will test Hypothesis H3*-*1 by means of multiple linear regression with the OPTION score as the outcome. Otherwise the analytical strategy will be identical to that in aim 1. Hypothesis H3*-*2 will be investigated by a logistic regression analysis with a dichotomous outcome indicating whether or not the subject’s preferred CRCS test option matched with the clinician’s recommendation. Once again the analytical strategy will be similar to that in aim 1. To investigate the independent effect of SDM on concordance, we will include the OPTION score as a covariate in the regression model. Hypothesis H3*-*3 will be studied by a multiple linear regression analysis with the patient intention after the patient-clinician encounter (post-encounter) as the outcome. The primary predictors in the model will be the study arm, the OPTION score, concordance, and the interaction between the OPTION score and concordance. The interaction term allows us to investigate any differential association within SDM and intention between the concordant and the discordant groups. The model will further be controlled for the patient intention before the patient-clinician encounter. The analytical strategy will be similar to that in aim 1.

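### The adjusted Aim 1 model conditions on the OPTION score, a post-randomisation mediator, so its arm coefficient is not the total effect named in H-1

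*Protocol article*

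**What the plan says.** Aim 1 tests H-1, that "patients in the intervention arm will have higher rates of CRCS adherence at the six month follow-up than those in the control arm". Under Analysis, Aim 1, completion is compared in two ways: "by means of a chi-square test (unadjusted analysis") and by "a logistic regression adjusting for potential predictors at baseline". The regression carries a practice indicator and uses generalised estimating equations for clustering by clinician. Later in the same paragraph comes the sentence at issue: "We will also adjust for OPTION score and pertinent clinician-level covariates". It is stated as a commitment, not as a candidate for screening.

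On timing, the randomisation section says "After completing the patient baseline survey, the computer program will randomize the patients". The section on audio recording and the OPTION scale has observers score OPTION from the recorded visit, which follows the web session.

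On the role of shared decision making, the Background says of the route from the decision aid to screening: "This process is also mediated by what occurs between the patient and the clinician during the clinic visit to discuss CRCS". It then names the degree of shared decision making as part of this. The abstract's central hypothesis gives the same route, and Table 2 lists shared decision making among its mediators and outcomes. H3-1 predicts that the arm changes it, with OPTION as the dependent variable.

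Variable selection retains a covariate if it is significant or if it would "change the co-efficient of the study arm variable by more than 5"%.

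**The concern.** H-1 is about the whole effect of assignment to the decision aid on screening. A model that holds OPTION fixed compares patients in the two arms who had the same degree of shared decision making, and so takes out whatever the decision aid achieves through that route. The loss is largest when the trial's central hypothesis is true.

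What remains is not a clean direct effect either. OPTION is not randomised, so anything that drives both shared decision making and screening (an engaged patient, for example) can bias the arm coefficient once OPTION is in the model.

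The section also contradicts itself: it describes the regression as adjusting for baseline predictors, then adds a variable that does not exist at baseline. For H3-2 the article gives a reason for including OPTION, namely its independent effect on concordance. For Aim 1 it gives none, and mediation already has its own place in the structural equation analysis.

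**Working it through.** **1. The plan's own figure.** Inputs from Sample size and power: 24% against 39%, two-sided 5%, 90% power, continuity-corrected chi-square. The mean rate is 0.315.

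- Uncorrected: n = [1.960·√(2·0.315·0.685) + 1.282·√(0.24·0.76 + 0.39·0.61)]² / 0.15² = (1.2875 + 0.8308)² / 0.0225 = 199.4, so 200.
- Corrected: (199.4/4)·[1 + √(1 + 4/(199.4·0.15))]² = 212.6, so 213 per arm. The stated figure reproduces.
- Corrected power at 300 per arm: Φ[(0.15 − 1/300 − 1.960·0.03793)/0.03743] = Φ(1.93) = 97%.

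These figures concern the total effect in an unadjusted comparison. Removing OPTION from the regression leaves them unchanged.

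**2. Order of events.** Baseline survey, randomisation, web session, recorded visit (OPTION), six-month chart audit. OPTION lies between the arm and the outcome.

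**3. Size of the attenuation.** Two quantities are needed that the documents do not give: the effect of the arm on OPTION (d, in SD) and the odds ratio for screening per SD of OPTION. Both are assumed here. Model: OPTION ~ N(d·arm, 1) and logit P(screened) = a + b·arm + ln(OR)·OPTION, with a and b set so that the marginal rates are 24% and 39%. The crude log-odds ratio is ln[(0.39/0.61)/(0.24/0.76)] = 0.705. Simulation used 300 per arm and 1,500 trials per setting. Without OPTION in the model, power is about 98% throughout.

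| d (SD) | OR per SD | Shrinkage of arm log-OR | Power with OPTION in model |
|---|---|---|---|
| 0.2 | 1.3 | 6% | 96% |
| 0.2 | 2.0 | 10% | 93% |
| 0.4 | 1.5 | 19% | 88% |
| 0.4 | 2.0 | 29% | 75% |
| 0.5 | 1.5 | 25% | 83% |
| 0.5 | 2.0 | 40% | 60% |

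Repeat runs of the last row give 39% to 40% shrinkage and 60% to 63% power.

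A hand check for d = 0.4, OR = 1.5: with d = 0 the OPTION-adjusted log-OR is 0.732. The part through OPTION is 0.4·ln 1.5 = 0.162. The remainder is 0.732 − 0.162 = 0.570, and the simulation gives 0.572. With d = 0 there is no attenuation.

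**4. Common cause, no true effect.** Screening is 24% in both arms, d = 0.4 SD, and an unmeasured trait affects both OPTION and screening (2,000 trials per setting; strengths assumed).

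- Trait correlated 0.3 with OPTION, log-odds 0.5 per SD on screening: adjusted OR 0.94; 5.0% of trials significant against the decision aid and 1.2% in its favour.
- Correlation 0.6, log-odds 0.8: adjusted OR 0.83; 14.3% against and 0.1% in favour.

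The nominal rate is 2.5% in each direction. The bias is towards a false signal of harm.

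**The case against.** The strongest reply is that the total effect is not lost. The chi-square test contains no OPTION, is named first, is the basis of the sample size, and uses an outcome that the chart-audit section describes as having no missing data. This stands, and it limits the point. But no sentence makes the chi-square primary, and only the regression deals with practice and clinician clustering, so its arm coefficient could well be read as the definitive answer to H-1.

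The attenuation also rests wholly on assumed inputs. Four of the nine combinations of 0.2, 0.4 and 0.5 SD with odds ratios of 1.3, 1.5 and 2.0 keep at least 90% power. Power drops below 80% only with an odds ratio of 2.0 and at least 0.4 SD.

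A reader might infer four further things that the documents do not support:

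- That H3-1 has OPTION on both sides. Aim 3 names OPTION as the outcome and then says "Otherwise the analytical strategy will be identical to that in aim 1". The word otherwise already excepts it.
- That patients without an OPTION score are dropped. Handling missing data imputes missing covariates. Nor does a recorder switched off for a sensitive topic mean that the screening discussion went unrecorded, and no rate is given. What stands is that adjusting for OPTION can bring avoidable imputation into an analysis with a complete outcome.
- That the 5% rule makes matters worse. OPTION enters as a stated adjustment, so the rule neither adds nor removes it. The rule simply gives no protection, because a mediator moves the arm coefficient as a confounder does.
- That the adjustment inflates false claims of benefit. In the common-cause case above, they fall below the nominal rate.

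**Conclusion.** The point holds for the adjusted H-1 regression. As written, its arm coefficient estimates an effect not passing through shared decision making, possibly biased by common causes, and the adjustment contradicts the section's own description of a baseline-adjusted model. Over the assumed ranges (0.2 to 0.5 SD; odds ratio 1.3 to 2.0 per SD), the log-odds ratio shrinks by about 6% to 40%, and power falls from about 98% to between 96% and about 60%. If the decision aid leaves OPTION unchanged, nothing is lost. It would be too strong to say that the trial cannot estimate its total effect, since the chi-square test does so. The defect is a second, unranked analysis of a primary outcome that answers a different question from the one posed.

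**What to change.** - Delete OPTION, and any other post-randomisation variable, from the H-1 effect model and from the candidates for covariate screening. The tool-completion factor in the same section is also post-randomisation and belongs in a separate model.
- Keep arm, practice, the other stratification factors (gender and race), baseline patient covariates, the clinician-survey covariates (collected at practice recruitment, before patients are randomised), and generalised estimating equations for clustering by clinician.
- For the question of how the decision aid affects screening, use OPTION only in the mediation and structural equation analysis, and state that the arm coefficient of an OPTION-adjusted model is not the effect of the decision aid.
- Leave the H3-1 wording as it is.

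The cost is analysis-plan wording only. The 213 per arm and the target of 300 do not change. The article reports recruitment still open in October 2013 and analysis planned from April 2015.
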